# Reducing antibiotic use for uncomplicated urinary tract infection in general practice by treatment with uva-ursi (REGATTA) – a double-blind, randomized, controlled comparative effectiveness trial

**DOI:** 10.1186/s12906-018-2266-x

**Published:** 2018-07-03

**Keywords:** Comparative effectiveness design, *Arctostaphylos uva-ursi*, Antibiotic prescription, General practice, Herbal remedy

## Abstract

**Background:**

Uncomplicated urinary tract infections (UTI) are common in general practice and usually treated with antibiotics. This contributes to increasing resistance rates of uropathogenic bacteria. A previous trial showed a reduction of antibiotic use in women with UTI by initial symptomatic treatment with ibuprofen. However, this treatment strategy is not suitable for all women equally. *Arctostaphylos uva-ursi* (UU, bearberry extract arbutin) is a potential alternative treatment. This study aims at investigating whether an initial treatment with UU in women with UTI can reduce antibiotic use without significantly increasing the symptom burden or rate of complications.

**Methods:**

This is a double-blind, randomized, and controlled comparative effectiveness trial. Women between 18 and 75 years with suspected UTI and at least two of the symptoms dysuria, urgency, frequency or lower abdominal pain will be assessed for eligibility in general practice and enrolled into the trial. Participants will receive either a defined daily dose of 3 × 2 arbutin 105 mg for 5 days (intervention) or fosfomycin 3 g once (control). Antibiotic therapy will be provided in the intervention group only if needed, i.e. for women with worsening or persistent symptoms. Two co-primary outcomes are the number of all antibiotic courses regardless of the medical indication from day 0–28, and the symptom burden, defined as a weighted sum of the daily total symptom scores from day 0–7. The trial result is considered positive if superiority of initial treatment with UU is demonstrated with reference to the co-primary outcome number of antibiotic courses and non-inferiority of initial treatment with UU with reference to the co-primary outcome symptom burden.

**Discussion:**

The trial’s aim is to investigate whether initial treatment with UU is a safe and effective alternative treatment strategy in women with UTI. In that case, the results might change the existing treatment strategy in general practice by promoting delayed prescription of antibiotics and a reduction of antibiotic use in primary care.

**Trial registration:**

EudraCT: 2016–000477-21. Clinical trials.gov: NCT03151603 (registered: 10 May 2017).

## Background

Acute urinary tract infections (UTI) represent a common condition in general practice and are usually treated with antibiotics. Though known to be self-limiting in many cases [1–5], UTI account for a significant number of antibiotic prescriptions [6]. This contributes to increasing resistance rates in UTI uropathogenic bacteria and is being discussed critically [7].

Antibiotic prescriptions can be problematic with regard to resistance rates, side effects and costs [8]. Furthermore, several studies show that women with uncomplicated UTI are often willing to delay or even decline antibiotic treatment because they are aware of possible adverse events [5, 9]. Considering these factors, there is a need for evidence of alternative treatment strategies in women with uncomplicated UTI.

In a recent trial, the strategy of initial symptomatic treatment with ibuprofen was proven to be effective in women with uncomplicated UTI and mild to moderate symptom burden [10]. Currently, another randomized controlled trial is being conducted by Vik and colleagues comparing ibuprofen versus mecillinam for uncomplicated cystitis [11]. Since ibuprofen is not suitable for all women equally, other treatment strategies should be explored alternatively. *Arctostaphylos uva-ursi* (UU, bearberry extract arbutin) has traditionally been used to treat UTI symptoms. Former studies have shown antiseptic and antimicrobial properties of UU which are attributed to hydroquinones and tannins [12]. UU is concentrated in the urine and has shown efficacy against bacteria causing UTI [13]. It is safe, only mild adverse events (AE) have been described previously (i.e. gastrointestinal complaints) and detailed investigation did not reveal any toxicity related to the ingestion of UU [14, 15]. In over the counter use, patients should be advised to respect recommended dosage and duration [16]. Being a herbal preparation, a generally high acceptance of UU by patients may be presumed [17]. Limited clinical data from small studies suggest that UU is effective in preventing UTI even in high risk patients [15, 18]. However, its clinical effectiveness in treating acute uncomplicated UTI and its potential to reduce antibiotic use has not yet been subject of a fully powered randomized controlled trial.

The main research questions of this study are:Does initial treatment with UU in women with uncomplicated UTI (starting treatment with UU and prescribing antibiotics only if symptoms persist) reduce the number of antibiotic courses without significantly increasing symptom burden?Is the suggested strategy safe with regard to complications and recurrences?

## Methods

The study protocol of REGATTA is based on the previous trial “Ibuprofen versus fosfomycin for uncomplicated urinary tract infection in women: randomised controlled trial” (ICUTI) [10].

### Study design

REGATTA is a double-blind, randomized, controlled comparative effectiveness trial with active control and parallel groups comparing initial herbal treatment of uncomplicated UTI with immediate antibiotic therapy.

### Trial objectives

#### Co-primary endpoints

Two co-primary endpoints are: 1) number of antibiotic courses day 0–28 and 2) symptom burden (AUC) day 0–7, defined as a weighted sum of the daily total symptom scores, measured as the area under the curve (AUC) of the total symptom score. The trial result is considered positive if superiority of initial treatment with UU is demonstrated with reference to the co-primary outcome number of antibiotic courses and non-inferiority of initial treatment with UU with reference to the co-primary outcome symptom burden. We assume non-inferiority if the symptom burden under UU is increased by less than 25% in comparison to the active control.

#### Key secondary endpoints

With reference to effectiveness: number of early relapses defined as recurrent symptoms until day 14 after initial symptom resolution, number of patients with recurrent UTI day 15–28, defined as recurrent UTI symptoms after initial symptom resolution, number of patients with symptom resolution on day 4 and 7, mean daily symptom sum scores day 0–7, symptom burden (AUC) for individual symptoms (dysuria, urgency, frequency, lower abdominal pain) day 0–7, symptom burden (AUC) day 0–7 of patients with positive and patients with negative urine culture, activity impairment by UTI symptoms days 0–7 (AUC), use of painkillers (defined daily dose, DDD) day 0–7, number of patients taking painkillers, antibiotic use (DDD) day 0–28, number of UTI related visits day 0–28, number of days of UTI related sick leave day 0–28.

With reference to safety: number of patients with temperature > 38 °C day 0–7, number of patients with worsening symptoms, number of patients with prolonged symptoms (> 7 days after inclusion), episodes of pyelonephritis day 0–28 according to general practitioner’s (GP) diagnosis, number of AE and SAE by system organ class day 0–28, proportion of patients with at least 1 AE / 2 AE. All patients will be followed up until symptom resolution. Symptom resolution is defined as max. One score point on each symptom scale.

### Sample size

Demonstrating non-inferiority regarding co-primary endpoint symptom burden drives the sample size. Based on data of the ICUTI trial [10], it was assumed that the coefficient of variation of symptom burden will be 70%. With this coefficient of variation the sample size required to demonstrate non-inferiority as defined above at a one-sided significance level of 2.5% with a power of 90% will be 170 patients per group, i.e. Three hundred forty patients in total give no difference in symptom burden between the groups. A Wilcoxon rank sum test comparing the two treatment groups with regard to the co-primary endpoint number of antibiotic courses has a power of at least 90% given the sample size of 170 patients per group and a probability of at least 61% that a patient in the intervention group takes fewer antibiotic courses than a patient in the control group. This is a conservative assumption as this probability was estimated to be in excess of 80% from data in the ICUTI study [10]. Adjusting for a drop-out rate of 20%, 430 patients have to be randomized. The sample sizes were calculated using nQuery Advisor® Version 7.0.

### Trial population

#### Setting and recruitment

General practices in Germany (Lower Saxony, Hesse, North-Rhine Westphalia, Thuringia and Bremen) will participate in the trial and recruit 430 patients during a 16 months recruitment period. The academic study centers in Göttingen and Hannover will provide structured practice support to optimize patient recruitment with newsletters, telephone calls and incentives.

On site monitoring visits are planned at the beginning and during the study for source data verification and to ensure correct procedures and documentation.

#### Inclusion and exclusion criteria

Women between 18 and 75 years with suspected UTI presenting at general practice with at least two of the following symptoms: dysuria, urgency, frequency and lower abdominal pain will be asked for participation, assessed for eligibility and included after written informed consent.

Key exclusion criteria comprise any signs of complicated UTI (i.e. temperature > 38 °C, loin tenderness), any conditions that may lead to complicated infections (i.e. renal diseases, patients with urinary catheter), pregnancy or breastfeeding, current self-medication with UU preparations, antibiotic use in the last 7 days, previous UTI in the past 2 weeks, history of pyelonephritis, contraindications for trial drugs, severe diseases (i.e. serious infection, multiple sclerosis), inability to understand trial information, and current participation in another clinical trial.

#### Trial drug and interventions

UU is a dry extract (dry extract ratio 2.5–4.5:1), extraction solvent water, containing 20–28% of hydroquinone derivatives calculated as anhydrous arbutin (spectrophotometry). The dosage for UU will be 3 × 2 105 mg arbutin for 5–6 days until all tablets have been completed. This will give a daily total of 630 mg arbutin, which is below the maximum dose of 840 mg as recommended by the European Medicines Agency (EMA). Haupt Pharma Wülfing GmbH, Member of the Aenova Group, is charged with the production of the UU tablets (Arctuvan®) and with the repacking of the tablets in new blisters. Six tablets will be packed in a blister and 5 blisters will be packed into a box. The blisters will be labeled by the Hospital Pharmacy of the University Hospital of Schleswig-Holstein (UKSH) who will prepare the drug as a clinical trial product. The shelf life is 3 years.

After written informed consent, patients receive either antibiotic therapy with fosfomycin 1 × 3 g or initial treatment with UU tablets (3 × 2 105 mg arbutin) for 5 days. In case of persistent or worsening symptoms, specific antibiotic treatment in line with the results of the urine culture can be initiated at the discretion of the GP. Since fosfomycin is only orally available as granules, a double dummy design is planned. The intervention group takes placebo granule sachets once additional to UU tablets (3 × 2 105 mg arbutin) whereas the control group takes placebo tablets 3 × 2 for 5 days additional to fosfomycin. Patients will be instructed to take preexisting co-medication as usual. Co-medication as well as any analgesics or other additional drugs will be documented in the electronic case report form (eCRF).

Randomization will be performed on patient level. Drug units will be labelled with code numbers from a computer generated random list. At inclusion, patients receive a drug unit, and the code number from the drug unit will be assigned to the patient.

### Clinical trial procedures

At inclusion (day 0), patients complete a symptom questionnaire after informed consent. Further, patients provide a urine specimen for dipstick, culture and pregnancy test, and body temperature will be taken in the ear or orally. GPs hand over the drug unit and recommend patients to visit again if symptoms persist or worsen or if fever occurs. If patients return therapy will be changed at the discretion of the GP and according to the German UTI guideline [19], results of the microbiological tests will be available after 4–5 days. Native urine samples will be stored in the refrigerator max. 24 h until collection to the laboratory. All urine cultures will be performed in one central laboratory.

### Data collection and management

Participant timeline in REGATTA with information on schedule for enrolment, interventions, assessments, and visits is provided in Table 1.

**Table 1 Tab1:** Participant timeline in REGATTA

Activity	Patient Contact	Baseline	Follow-up							
Day		0	1	2	3	4	5	6	7	28
Visit Number		I								II
Screening		X								
Informed Consent		X								
Inclusion / Exclusion criteria		X								
Medical History, Examination		X								
Urine Tests^a^		X								
Pregnancy Test		X								
Drug Intake^b^		X	X	X	X	X	X			
Symptom Assessment and Activity Impairment (Diary)		X	X	X	X	X	X	X	X	
Additional Antibiotic Courses			X	X	X	X	X	X	X	X
Painkiller Intake			X	X	X	X	X	X	X	X
Adverse Events and Complications			X	X	X	X	X	X	X	X
Recurrent UTI (Questionnaire)										X
Return of Drug Packages										X
Phone Calls to Remind Patients (Diary, Drug Return, Questionnaire)			X						X	X

^a^Midstream urine for on-site dipstick test (leukocytes, nitrite, red blood cells) and for urine culture (pathogens and resistances)

^b^Drug intake until all 30 tablets are finished (= 3 × 2 tablets uva-ursi daily for 5 days)

#### Inclusion: Symptom questionnaire

Patients will complete a symptom questionnaire which has been used in previous UTI studies but has not been validated yet [4, 10]. Duration and severity of symptoms and activity impairment will be documented. Symptom evaluation will cover the symptoms dysuria, urgency, frequency and lower abdominal pain, each scored from 0 (none) to 4 (very strong). UTI-related activity impairment covers impairment by each single symptom (see above), scored as well from 0 (none) to 4 (very strong) [20]. Data will be transferred to the web-based eCRF by practice staff.

#### Follow-up

Patients will be asked to record daily symptom severity and activity impairment in the patient diary for at least 7 days. Additionally, pain killer intake and any antibiotic treatment between day 0–7 will be documented. The diaries will be sent back by the patients to the general practice. There will be a follow-up documentation on day 28, where patients will complete the follow-up survey including antibiotic intake, relapses and recurrent UTI, AEs/SAEs, UTI-related consultations and days of sick leave. Study nurses will transfer these data to the web-based eCRF.

### Statistical analysis and reporting

The primary analysis will be based on the results of two statistical tests corresponding to two co-primary endpoints. The first test will be on the following two hypotheses H0 (H1): The rate of antibiotic courses per patient within the interval 0–28 days in the UU group is greater or equal (lower) than the rate in the fosfomycin group. The second test will be on the following two hypotheses: H0 (H1): The symptom burden within the interval 0–7 days in the UU group is greater or equal (lower) than 125% of the corresponding symptom burden in the fosfomycin group. Since both criteria have to be fulfilled for the study to be positive, both hypotheses are tested at a one-sided level of 2.5% and the overall type I error rate will still be controlled at the one-sided level of 2.5% (intersection-union method).

The number of antibiotic courses within the interval 0–28 days will be compared between treatment groups using a Wilcoxon rank sum test. The treatment effect will be reported in terms of the so-called relative effect (or also probabilistic index) with 95% confidence interval [21]. As supporting analyses, the number of antibiotic courses will be modelled using suitable parametric models such as negative binomial regressions with treatment group and study center as factors and baseline symptom score as covariate.

An analysis of covariance (ANCOVA) of log symptom burden will be performed with the treatment group as factor and the day-0 (inclusion) log sum of symptom scores as covariate. From this model, a two-sided 95% confidence interval for the ratio of the expected total symptom burden of conditional antibiotic use vs. immediate use will be derived and compared to the non-inferiority margin of 125%.

Secondary endpoints will be explored using regression models appropriate for type of scale, without adjustment for multiplicity.

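### Co-primary 1 states its hypotheses for the rate of antibiotic courses, but the test, power statement and estimate address the relative effect, so the 2.5% level does not hold for the null as written

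*Protocol article*

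**What the plan says.** All of the following stands in the protocol article.

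- **Hypotheses** (Statistical analysis and reporting): "The rate of antibiotic courses per patient within the interval 0–28 days in the UU group is greater or equal (lower) than" the corresponding rate under fosfomycin.
- **Test** (same section): the number of courses "will be compared between treatment groups using a Wilcoxon rank sum test".
- **Estimate** (same section): "The treatment effect will be reported in terms of the so-called relative effect (or also probabilistic index") with a 95% confidence interval.
- **Rate models** (same section): "As supporting analyses, the number of antibiotic courses will be modelled using suitable parametric models such as negative binomial regressions".
- **Error claim** (same section): "both hypotheses are tested at a one-sided level of 2.5"%, and by the intersection-union method "the overall type I error rate will still be controlled at the one-sided level of 2.5"%.
- **Power** (Sample size): at least 90% for the Wilcoxon test with 170 per group, if the probability that a UU patient takes fewer courses than a control patient is at least 61%. The predecessor trial is said to suggest more than 80%.
- **What is counted** (Abstract, Methods): "Two co-primary outcomes are the number of all antibiotic courses regardless of the medical indication from day 0–28".
- **Control treatment** (Trial drug and interventions): "patients receive either antibiotic therapy with fosfomycin" or initial UU tablets.

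**The concern.** The rate of courses per patient is most naturally read as the mean count. The Wilcoxon test responds to a different quantity, the relative effect: the probability that a UU patient has fewer courses than a control patient, plus half the probability of a tie. The two nulls agree if the arms differ only by a shift, but this design makes a pure shift implausible near the null. If fosfomycin at inclusion counts, controls start at one course while UU patients can have none. Equal means then require other UU patients to have more courses than controls, so the two distributions cannot have the same shape.

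Two things follow. First, the test can reject when the mean rates are equal, so it does not test the null as written. Second, the standard Wilcoxon variance assumes identical distributions, so even at relative effect 0.5 the level is not exactly 2.5%. The intersection-union argument needs each component test to hold 2.5% for its own null. At stake are the stated error control and the claim that a significant result may support.

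**Working it through.** **1. The plan's own figure.** Noether's formula gives power = Φ(√(6n)·(p − 0.5) − 1.96) for n per group. With n = 170 and p = 0.61: √1020 × 0.11 − 1.96 = 1.55, so power is 94%. The claim of at least 90% holds.

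**2. Inputs for the level check.** n = 170 per arm and one-sided 2.5% come from the protocol. It gives no course distributions, so those below are assumptions. All controls are set to one course.

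**3. Formulas.** With controls fixed at 1, score each UU patient g = 1 for no course, 0.5 for one and 0 for more.

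- The estimated relative effect is the mean of g. Its true variance is V/170, with V = E(g²) − (E g)².
- The tie-corrected Wilcoxon variance is W/170, with W ≈ 341/(12 × 170) × (1 − Σq³) = 0.1672 × (1 − Σq³), where q are the pooled category shares.
- Rejection probability ≈ 1 − Φ[(0.5 + 1.96·√(W/170) − E g)/√(V/170)].

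**4. Relative effect exactly 0.5 (means also equal at 1.0).**

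- UU 40/20/40% with 0/1/2 courses: V = 0.40 + 0.05 − 0.25 = 0.20. Pooled shares are 0.2/0.6/0.2, so W = 0.1672 × 0.768 = 0.128. The SE ratio is √(0.20/0.128) = 1.25 and the size is 1 − Φ(1.96/1.25) = 5.8%.
- UU 30/40/30%: V = 0.15, W = 0.1672 × 0.650 = 0.109, SE ratio 1.17, size 4.8%.

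Simulation with 200,000 trials gives 5.7% and 4.8% for Wilcoxon, and 2.6% in both cases for Brunner-Munzel.

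**5. Equal means, skewed UU arm.** UU 40/30/20/10% with 0/1/2/3 courses has mean 0.30 + 0.40 + 0.30 = 1.0, as in controls.

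- The relative effect is 0.40 + 0.15 = 0.55, with V = 0.40 + 0.075 − 0.3025 = 0.1725 and W = 0.1672 × 0.716 = 0.120.
- The Wilcoxon rejection limit is 0.5 + 1.96·√(0.120/170) = 0.552 and the true SE is √(0.1725/170) = 0.0319. The rejection probability is about 47% (48% simulated).
- An unequal-variance test of means rejects 3.0% of the time (simulated).
- Brunner-Munzel rejects about 35%: 1 − Φ[(1.96 × 0.0319 − 0.05)/0.0319]. It corrects the variance but does not turn a rank test into a test of the rate.

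**6. How extreme are these cases?** With a control mean of 1.0 and a share p₀ of UU patients with no course, equal means require the other UU patients to average 1/(1 − p₀) courses in 28 days. That is 1.43 at p₀ = 30%, 1.67 at 40% and 2.56 at 61%.

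**7. Near the expected effect.** Take UU 62/30/8% with 0/1/2 courses and controls at 1, so the relative effect is 0.62 + 0.15 = 0.77. Then V = 0.102 (SE 0.0245) and W = 0.116 (SE 0.0261). The Wilcoxon SE is now slightly too large and z is about 0.27/0.0261 = 10. Wilcoxon, Brunner-Munzel and the test of means all have power near 100%.

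**The case against.** The strongest defence is that one word carries the problem. The article does not define rate as a mean, it elsewhere calls the endpoint a number of courses, and power, test and estimate share one target. On that reading the 48% is no error: the relative effect there is 0.55, and the test detects a real difference in what the protocol powers and reports. The defence adds that the null scenarios need many repeat courses within 28 days, that a positive trial also needs non-inferiority on symptom burden, and that a negative binomial model of the counts is already planned.

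Most of this stands, and it limits the size of the point. It does not remove the point. The hypotheses are the formal statement to which the 2.5% is attached, and they name a rate. Reading them as a relative effect would still leave a level of about 5-6% in step 4.

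A reader might infer more than the documents support:

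- **That every control patient certainly has at least one course.** This is inferred from the design. No passage says outright that trial fosfomycin is counted, and Table 1 lists additional courses. The predecessor figure above 80% makes counting very probable, but non-takers and drop-outs are possible.
- **That the relative effect is yet another target.** It is what the Wilcoxon test addresses. Only the variance may differ, and the interval method lies in a cited source that is not shown.
- **That the trial faces a false-positive risk near 48%.** That figure concerns one component test, one assumed distribution and the mean reading of rate.

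**Conclusion.** The mismatch is real. The hypotheses concern a rate, while everything used to decide on them concerns the relative effect. A significant Wilcoxon result would not by itself establish a lower rate, and the 2.5% claim does not hold for the null as written. Under the assumed distributions the level is about 5-6% at relative effect 0.5, and rejection reaches about 48% at equal means in the skewed case shown. The figures rest on 170 per arm, controls at one course each, and UU distributions that the documents do not supply. The expected probability above 80% is far from these nulls, and there all tests agree, so the trial's conclusion is unlikely to change. Severity is minor to moderate.

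**What to change.** Align hypothesis, test and estimate on the quantity already used for power and reporting:

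1. Restate the null of co-primary 1 as relative effect ≤ 0.5, oriented so that values above 0.5 mean fewer courses under UU.
2. Test it with the Brunner-Munzel test, and derive the relative-effect confidence interval from the same variance, which is valid under unequal distributions.
3. Keep the rate model as a supporting analysis, with a robust variance.
4. State explicitly that the randomized fosfomycin dose counts as a course, if that is intended.

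If the trial is meant to claim a lower mean rate, make a rate ratio or mean difference with robust variance the primary test instead, and report the relative effect as supportive. Changing only the test to Brunner-Munzel while leaving the rate hypothesis in place would not be enough (step 5).

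The cost is a change of analysis wording. It needs no additional patients and loses no meaningful power at the expected effect.
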